**LIST OF ABBREVIATIONS AND RELEVANT DEFINITIONS**

| **ABR** | **ABR form (General Assessment and Registration form) is the application form that is required for submission to the accredited Ethics Committee (ABR = Algemene Beoordeling en Registratie)** |
| --- | --- |
| **AE** | **Adverse Event** |
| **AR** | **Adverse Reaction** |
| **CA** | **Competent Authority** |
| **CCMO** | **Central Committee on Research Involving Human Subjects** |
| **CV** | **Curriculum Vitae** |
| **DSMB** | **Data Safety Monitoring Board** |
| **EU** | **European Union** |
| **EudraCT** | **European drug regulatory affairs Clinical Trials GCP Good Clinical Practice** |
| **IB** | **Investigator’s Brochure** |
| **IC** | **Informed Consent** |
| **IMP** | **Investigational Medicinal Product** |
| **IMPD** | **Investigational Medicinal Product Dossier** |
| **METC** | **Medical research ethics committee (MREC); in Dutch: medisch ethische toetsing commissie (METC)** |
| **(S)AE** | **Serious Adverse Event** |
| **SPC** | **Summary of Product Characteristics (in Dutch: officiële productinfomatie IB1-tekst)** |
| **Sponsor** | **The sponsor is the party that commissions the organisation or performance of the research, for example a pharmaceutical**  **company, academic hospital, scientific organisation or investigator. A party that provides funding for a study but does not commission it is not regarded as the sponsor, but referred to as a subsidising party.** |
| **SUSAR** | **Suspected Unexpected Serious Adverse Reaction** |
| **Wbp** | **Personal Data Protection Act (in Dutch: Wet Bescherming Persoonsgevens)** |
| **WMO** | **Medical Research Involving Human Subjects Act (Wet Medisch-wetenschappelijk Onderzoek met Mensen** |

**SUMMARY**

**Rationale:** Since the incidence of whooping cough (pertussis) is increasing in the Netherlands, the effect of vaccination against *Bordetella pertussis* needs to be addressed.

Because of the increasing incidence of whooping cough at the age of 4, an acellular booster vaccination (ACV) at 4 years of age is introduced in the Netherlands in 2001. However, nowadays the peak incidence of whooping cough in children has shifted to 8-9 years old children. In addition, we also see a rise in notifications in adolescents and adults. Therefore, in some countries, e.g. Germany and France, an extra acellular booster vaccination has been given to the 9-14 years old children. Also in Belgium they will introduce an extra booster vaccination in 14-16 years old children. Because of the shift in the prevalence peak, the effect of the booster vaccination on the long term immunity against *Bordetella pertussis* needs to be addressed in this specific age group.

This study aims to investigate the longitudinal kinetics of the effect of the ACV booster vaccination on the memory B- and T- cell immunity in children who are primary vaccinated with whole cell vaccine (WCV) and boostered with ACV at 4 years old. Furthermore, the relationship between the cellular immunity and the antibody responses after ACV booster will be addressed in order to gain insight if further booster vaccinations are required.

**Objective:** The assessment of the duration of the cellular immunity to *Bordetella pertussis* after an extra ACV booster and the relationship between the memory B- cells and antibody responses.

The methods used in the study are:

B- and T- cell memory responses and antibody levels against the various components present in the acellular pertussis vaccine.

**Study design:** Intervention study: An extra ACV booster vaccination will be given to children of 8-9 years old. One pre-vaccination blood sample will be taken and two post-vaccination blood samples will be taken at 28 days and 1 year in which the frequency of memory B- cells will be assessed. Questionnaires including questions concerning clinical manifestations of whooping cough will also be completed. A control group including children of the same age who received the ‘normal’ DTP but did not receive the extra ACV booster at age 8-9 years will be included. One blood sample will be taken one year after the ‘regular’ DTP vaccination.

**Study population:**  A population of 8-9 years old children who received four vaccinations at 2,3,4 and 11 months with DT**Pwcv**-IPV-(Hib) and a booster vaccination at 4 years old with a three component ACV will be recruited.

**Intervention:** The combination vaccine DTPacv-IPV (Boostrix polioTM) produced by GSK containing a 3 component ACV (Pertussis toxin (Ptx), filamentous hemagglutinin (FHA) and pertactin (Prn), tetanus toxoid, diphtheria toxoid and inactivated polio virus, will be given 8-9 years old children who received the DT**Pwcv**-IPV-(Hib) at 2,3,4 and 11 months old and DTP + a three component ACV (Monovalent ACV by GlaxoSmithKline (GSK)) as a booster vaccination at 4 years old. The extra pertussis vaccination is combined with the DT-IPV and MMR vaccination which they receive in the regular immunization program. One pre- and two post-vaccination (28 days and 1 year) blood samples will be taken. In the control group one bloodsample will be taken one year after the regular DTP-vaccination.

**Main study parameters/endpoints:** The main study parameters will be pertussis specific memory B- and T- cell responses as well as antibody levels and affinity against the various proteins of pertussis and the other components of the DT**Pacv**-IPV-Hib vaccine.

**Nature and extent of the burden and risks associated with participation, group relatedness:**

Memory B- and T- cell immunity and the relationship between memory B- cells and antibody responses after a booster with an acellular pertussis vaccine will be addressed. This requires a blood sample of 15 ml per child pre- and post-vaccination (total of three blood samples) and for the control group one blood sample of 15 ml. A volume of 15 ml is needed to be able to do all the memory B- cell tests against the five most important proteins of *Bordetella pertussis*. With less material, B- cell responses against just one or two proteins of pertussis will be measured. A questionnaire will be used to relate immune functions to clinical manifestations of whooping cough.

We expect 5% of all parents to consent in participation based on our experiences with a previous study. The total number needed will be 70 children. For the control group 20 children will be included. There will be no risk for the participants.

**1. INTRODUCTION AND RATIONALE**

Pertussis is a serious disease caused by the bacterium *Bordetella pertussis (B. pertussis)* and more rarely by *Bordetella parapertussis*. Once *B. pertussis* has entered the host, it uses his adhesins to attach to cilia in the respiratory mucosa. When immunological constraints are absent, the organism will proliferate and it will begin to spread downward in the respiratory tract. During this time toxins are released, causing a highly contagious and severe infection of the respiratory tract (Weiss et al, 1996).

The detection of specific serum antibodies is the most widely applied method to investigate immunity against vaccine-preventable diseases like pertussis, although the presence of antibodies does not always confer protection for infection or disease. However, in large efficacy trials in Sweden and Germany both groups of investigators observed that the presence of antibodies against certain virulence factors of *B.pertussis* (in particular Pertussis toxin, Pertactin and Fimbriae) could be related to protection against whooping cough (Cherry et al 1998, Hewlett et al 1998, Storsaeter et al 1998). Nevertheless, antibodies decline very rapidly after booster vaccination against *B.pertussis*. This indicates increasing evidence for a central role of cellular mediated immunity against *B.pertussis*, although little data on that issue are available.

Moreover, since the peak incidence of whooping cough has moved from the 3-4 years old to the 9 years old, due to the introduction of the acellular booster vaccination at 4 years old, and the incidence of whooping cough also rises in adolescents and adults, the longitudinal kinetics of the effect of the acellular booster vaccine on the long term immunity needs to be addressed.

The pertussis vaccines are administered in the first year of life when the immune system is not yet fully developed and the (long term) effects of this major change in the vaccination program are not known.

This study aims to investigate the effect of an extra ACV booster vaccination on the longitudinal kinetics of the cellular immunity and antibody response, and to investigate a possible relation between the cellular and humoral immunity, in Dutch 8-9 years old children who are primarily vaccinated with the whole cell pertussis vaccination and boostered with the acellular pertussis vaccine at 4 years of age.

## Background

*B. pertussis* occupies the respiratory tract in humans. Previous studies indicate that both antibody-mediated and cellular immune mechanisms play a large role in protection against pertussis (Leef et al, 2000). Humoral antibody responses are largely measured to the vaccine-components pertactin (Prn), pertussis toxoid (Ptx), Filamentous hemaglutin (FHA) and fimbriae (Fim). These antigens neutralize, either have toxic effects or inhibit attachment of the bacterium to the epithelial cells.

The intracellular positioning of *B. pertussis* requires elimination of the cells that are infected; an activity, mainly associated with cellular immunity (Mills et al, 2001, Zepp et al, 1997).

Immunization using a vaccine composed of whole cells of killed *Bordetella pertussis* (WCV) bacteria was introduced in the National Immunization Programme (RVP) in 1957. In 1962 the combination vaccine DPwcvT-IPV was introduced. Since 1997 many changes have occurred in the pertussis vaccination in the National Immunization Program, which are listed below.

Changes in pertussis vaccination programme in the Netherlands since 1996

end of 1997: * 3,4,5 and 11 months: D**Pwcv**T-IPV + Hib potency 4 7 IU

1999: * 2,3,4 and 11 months: D**Pwcv**T-IPV + Hib adaptation schedule

2001: * 2,3,4 and 11 months: D**Pwcv**T-IPV + Hib

* 4 years booster: DT-IPV + **Pacv** Monovalent ACV (GSK)

2003: * 2,3,4 and 11 months: D**Pwcv**T-IPV-Hib combination

* 4 years booster: DT-IPV + **Pacv** Monovalent ACV (GSK)

2005: * 2,3,4 and 11 months: D**Pacv**T-IPV-Hib Infanrix-IPV-Hib (GSK)

HepB (SP)

* 4 jaar booster: DTP + **Pacv** Monovalent ACV (GSK)

2006: * 2,3,4 and 11 months: D**Pacv**T-IPV-Hib Pediacel (SP)

* 4 years booster: D**Pacv**T-IPV Triaxis (SP)

Infanrix Hexa (HepB)

2007: * 2,3,4 and 11 months: D**Pacv**T-IPV-Hib Pediacel (SP)

* 4 years booster: D**Pacv**T-IPV Triaxis (SP) /

Infanrix-IPV (GSK)

Nowadays, children are vaccinated at the age of 2, 3, 4, and 11 months with a tetravalent diphtheria, pertussis, tetanus and inactivated polio virus vaccine which is combined with a Hib vaccine (DTP-IPV-Hib) prior to vaccination (Labadie et al 1996). This mass vaccination has markedly decreased the incidence of pertussis and the mortality caused by the disease.

In the Netherlands, a rise in notifications of whooping cough is observed every 2-3 years since 1996 (de Greeff et al, 2004). As a response to the first epidemic of 1996-1997 two changes have been made in the RVP. Firstly, in 1997 the potency of the whole cell pertussis vaccine component was enhanced from 4 to 7 International Units and the production process has been changed in order to enlarge the Ptx content of the vaccine. Secondly, in 1999 the immunization schedule was shifted forward from 3, 4, 5 months to 2, 3, 4 months to provide protection for the neonates as early as possible.

Adverse reactions observed with WCV were a great stimulus for the development of ACVs, which reduced the severity and number of adverse reactions. In addition, as serological studies showed the presence of very low titers against pertussis antigens in children at the age of 4 years (Berbers et al, 1999), in 2001 it was decided to introduce an acellular booster at 4 years of age.

Since January 2005, because of the public commotion about the adverse reactions to WCV, all children receive DTPacv IPV-Hib vaccine (Infanrix-IPV) from GSK containing a 3 component ACV (Ptx, FHA and Prn) at 2,3,4 and 11 months of age. Since January 2006, the combination vaccine DTPacv-IPV-Hib (Pentacel) of Sanofi Pasteur containing a 5 component ACV (Ptx, FHA, Prn and Fim2 + 3) is used.

However, although antibody titers are higher after vaccination with ACV, they wane relatively fast to undetectable levels (Berbers et al, 1999) which indicates that cellular immunity plays an important role in maintaining long term immunity. Our ongoing study (Memory study, protocol number LTR 137) shows high antibody titers against the 5 pertussis antigens 1 month after acellular booster vaccination at 4 years of age. However, antibodies decrease 2 years after the acellular booster and more than 90% are below protection level at 9 years of age (Hendrikx et al, in progress).

Furthermore, when administering ACV, it appears that the type of immune response induced differs from children whom are vaccinated with WCV (Olin et al, 1997; Simondon et al, 1997).

Nowadays, the peak prevalence of whooping cough is noticed in 9 year old children and young adolescents, due to the booster at 4 years of age (De Greef et al, 2008). Therefore, in Germany and Sweden an extra ACV booster vaccination is given at 9-10 years of age ([www.euvac.net](http://www.euvac.net/)) and in France and Italy at 10-11 years of age. In Belgium they also will introduce an acellular booster vaccination at 14-16 years of age. The effect of an extra ACV at this age on the (long term) immunity is still unknown.

The immune system is still in development when the first vaccinations take place.

Vaccination against disease often aims for the production of high antibody titers, and adjuvants are regularly included for their capacity to induce antibody-mediated protection. This may however not be the most efficient immune response elicited. Evidence is accumulating that it is very important to elicit the right type of immune response when vaccinating individuals in order to be optimally protected. When aiming towards high antibody production it is important to realize to what extent antibodies mediate protection and the time period they remain protective. Growing insights in the immune system have revealed that the innate immune response has a regulating role in induction of memory B- cells as well as the different types of T- lymphocytes, which could have important implications for the development and production of a vaccine.

# This project aims to get insight in the long-term protective memory immunity against *B. pertussis* and the relationship between the cellular and antibody immune responses in children who completed the vaccination program and who will receive an extra booster with ACV. Therefore we will investigate the longitudinal kinetics of the effect of the ACV booster on the cellular memory immunity as well as the relation with the antibody response.

# 2. OBJECTIVES

Primary Objective:

To assess the longitudinal kinetics of the long term cellular immunity to *B. pertussis* after ACV and the relationship between the cellular (long term) immunity and antibody responses.

There is little knowledge of the cellular immune response against *B.pertussis* in Dutch children. These data are very relevant to obtain insight in the effect of vaccination on the long term protection against *B. pertussis* as well as the effect of changes in the vaccination program on the immune status of children.

The primary objective of this study is to get insight in the longitudinal kinetics of the B- and T- cellular memory immune responses against *B.pertussis* and the relationship with the antibody response induced after an extra booster vaccination with ACV at 8-9 years of age.

- Memory B- and T- cells will be isolated and after polyclonal stimulation will be tested against various proteins of B. pertussis.
- Antibody responses will be measured against the various proteins of B.pertussis.

Secondary Objective:

If there are enough lymphocytes, the immune response (memory B- and T-cells and antibody responses) to other vaccine preventable diseases, like measles, mumps, diphtheria, tetanus and polio will also be measured.

**3. Study design**

Interventional study with a single intervention (an extra DTPacv-IPV booster vaccination in the 8-9 years old children) and blood samples taken pre-vaccination and post-vaccination at 28 days and 1 year after the extra booster. The time window for the blood sample at 28 days will be  2 days and the time window for the blood sample 1 year after vaccination will be  2 weeks. A questionnaire will be taken about the clinical symptoms of whooping cough (annex 4).

A control group including children of the same age who did not receive the extra ACV booster at age 8-9 years will be included. One bloodsample will be taken one year after the ‘regular’ DTP vaccination.

# 4. STUDY POPULATION

## Population (base)

A population of healthy Dutch 8-9 years old children will be recruited. The children have already received four vaccinations at 2, 3, 4 and 11 months with DTPwcv-IPV-Hib and a booster vaccination with a three component ACV at 4 years.

## Inclusion criteria

Infants in good general health (eligible) who have been vaccinated according to the Dutch national immunization program.

Provision of written informed consent by both parents and legal representatives.

## 4.3 Exclusion criteria

## Any of the following criteria will exclude a volunteer from participation, at start of the study:

- Present evidence of serious disease(s) demanding immunosuppressive medical treatment, like corticosteroids that might interfere with the results of the study within 3 months.
- Any known primary or secondary immunodeficiency.
- Boostrix Polio must not be given to people with a known hypersensitivity after a former injection of diphteria-, tetanus-, pertussis- or poliomyelitis-vaccins or one of the substances of the vaccines.
- Boostrix Polio is contraindicated to people who suffered from an encephalopathy without a known cause within 7 days after a former pertussis vaccination.
- Boostrix Polio must not be administered to people who suffered from a temporary trombocytopathia or people who had neurologic complications (convulsions or hypotonehyporesponsive episodes) after a former administration with a diphtheria or tetanus vaccine.

Delay criteria

In case of a child is having fever (> 38,5oC) within 2 days before the vaccination will take place and before blood sampling, which can interfere with the cellular immune responses at that time, another appointment for the vaccination and/or blood sampling will be made. If the child has received another vaccine within a month before the vaccination and/or the blood sample will be taken, the vaccination and/or blood sample will be delayed too.

## Sample size calculation

This study is designed to investigate the direct as well as the long term effect of the acellular pertussis vaccine on the cellular immunity by measuring the cellular immune responses and the antibody titers after primary series and an extra booster vaccination.

Data on cellular immune responses against *B. pertussis* in Dutch children are not yet available.

An ongoing study that compares the effect of WCV and ACV on the long term cellular memory immunity against *B. pertussis* and the other components of the DTP-IPV-Hib vaccine in Dutch children, started in 2006 and aims for 60 children per age group. To compare these data with the data that will be attained in this study, we aim for a total of 60 children. However, we expect about 15% of the children to stop prematurely; therefore we aim for a total of 70 children.

For a control group we aim for 20 children. A group of 20 children of 10 years of age not being boostered with a pertussis vaccine at 9 years of age will be included in the study. If circulation of pertussis will be increased during the last year, the geomean antibody titers against pertussis toxin (PT) will be increased in our control group in 2010 compared to 9 years old children before booster vaccination in 2009. Moreover, in addition to PT antibody titers the percentage of PT specific memory B-cell responses will increase too due to a higher circulation of pertussis (Buisman et al, Vaccine 2009). However, a high increase in the circulation of pertussis is very unlikely.

Our previous studies in 2007 showed equal geometric mean antibody titres in children of 6 to 10 years of age, in groups of 60 children as well as in groups of 20 children. Therefore, the number of 20 children in this control group will be sufficient to calculate any effect of recent circulation of pertussis on pertussi toxin specific antibody titers or memory B-cell responses.

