### Specific criteria for withdrawal (if applicable) not applicable

## Replacement of individual subjects after withdrawal

## Because we expect 15% of all children to prematurely withdraw from the study, we aim for 70 children at the start of the study, so there will be 60 children completing the study. For the control group we aim for 20 children.

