Considering the available time span and the area’s where the study has to be performed it is realistic to aim for 45 children per group. Anticipating withdrawals and dropouts during the trial the objective is to include 60 children per group. This will allow us to observe a statistically significant difference between the different time-points before and after booster vaccination if we measure a twofold rise in the antibody titer against these antigens of the pertussis vaccine component.

For the control group we aim for 20 children who did not receive the extra ACV booster at age 8-9 years and who have the same age as the children under investigation in the study. One bloodsample will be taken one year after the regular DTP vaccination to exclude the effect of *Bordetella pertussis* circulation on the immunological parameters measured. Since pertussis antibody levels wane in 2-3 years after vaccination, high antibody levels will indicate a recent infection with *Bordetella pertussis* in this control group. For comparison of the results of the children who received the extra pertussis vaccination with this control group one-year post-vaccination, we will use an unpaired t-test. Antibody levels and cellular responses will be described in descriptive statistics and figures. In this way, we can improve the understanding of the vaccine effect on the immunological parameters measured.

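### The protocol calls 20 controls enough for any effect of pertussis circulation, but the variability implied by its own power statement supports only about a 2.5- to 3.3-fold PT difference at 90% power

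*Protocol*

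**What the plan says.** The control group was added by the first amendment. The Sample size calculation section sets its size ("For a control group we aim for 20 children") and its circulation question: PT geometric means in the controls in 2010 are set against the boosted cohort's own baseline, that is, "compared to 9 years old children before booster vaccination in 2009". The same section regards a large rise in circulation as very unlikely.

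The reason given for 20 is earlier work, dated 2007, that "showed equal geometric mean antibody titres in children of 6 to 10 years of age"; this is reported to have held "in groups of 60 children as well as in groups of 20 children". From this it concludes that "the number of 20 children in this control group will be sufficient to calculate any effect of recent circulation of pertussis" on PT titres or memory B-cell responses. It gives no SD, target difference or power for the 20.

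Section 9, Descriptive statistics, states the purpose of the sample: "One bloodsample will be taken one year after the regular DTP vaccination to exclude the effect of" *B. pertussis* circulation on the measured parameters. It also plans an unpaired t-test of boosted children against controls at one year, and it treats high titres in controls as a sign of recent infection. The protocol's only power statement is in the same section and concerns the earlier Memory study.

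**The concern.** Equal geometric means are a statement about location. They do not show how precisely a difference can be estimated, and small groups that fail to differ are also what low power produces. The conclusion about 20 children therefore does not follow from the reason given.

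The claim also sits badly with Section 9, where 45 children per group are said to need a 2.1- to 2.3-fold PT difference for 90% power. A group of 20 cannot be adequate for effects of every size. The weak region is the one that matters: if a large rise in circulation is unlikely, any effect that occurs is expected to be modest.

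What is at stake is mainly the reading of each boosted child's change from pre-vaccination to one year. That change mixes waning after the booster with any natural exposure during the year. If the control check is thought able to reveal any circulation effect, a modest one could pass unnoticed and be counted as persistence of the booster response.

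**Working it through.** **Inputs from the protocol**
- Controls: 20 (Sample size calculation).
- Comparator for the circulation question: the pre-booster sample. It is taken at the first visit, before withdrawals, so 70 children ("therefore we aim for a total of 70 children"). The figure of 60 ("so there will be 60 children completing the study") applies at one year.
- Power statement for PT in Section 9: 45 children per group, 90% power, 5% level, 2.3-fold using 90 former samples and 2.1-fold using 268.

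**Assumptions:** two-sided 5% (sidedness is not stated); unpaired t-test on log titres (the test for controls against baseline is not named); the same SD in both groups and in unboosted 9- to 10-year-olds.

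**Step 1. Reproduce the protocol's figures and recover the SD.**

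log10(fold) = SD × (1.960 + 1.282) × √(1/n1 + 1/n2), so SD = log10(fold) / [3.2415 × √(1/n1 + 1/n2)].

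The text can be read as 45 against 45, or as 45 new children against the former samples.

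| Stated PT fold | Reading | √(1/n1 + 1/n2) | Implied log10 SD |
|---|---|---|---|
| 2.1 | 45 v 45 | 0.2108 | 0.472 |
| 2.3 | 45 v 45 | 0.2108 | 0.529 |
| 2.3 | 45 v 90 | 0.1826 | 0.611 |
| 2.1 | 45 v 268 | 0.1611 | 0.617 |

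Under the second reading, one SD explains both figures. The 0.611 obtained from 2.3-fold predicts 10^(0.611 × 3.2415 × 0.1611) = 2.09-fold with 268 samples, against the stated 2.1. The first reading returns the stated figures only by construction. Both are kept as a range.

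**Step 2. Apply these SDs to 20 controls against 70 pre-booster children.**

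√(1/20 + 1/70) = 0.2535. By the normal formula, the ratio detectable with 90% power runs from 10^(0.472 × 3.2415 × 0.2535) = 2.44 to 10^(0.617 × 3.2415 × 0.2535) = 3.21. With the noncentral t distribution (88 degrees of freedom):

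| log10 SD | Ratio at 90% power | Ratio at 80% power | Power for 2-fold | Power for 1.5-fold |
|---|---|---|---|---|
| 0.472 | 2.47 | 2.18 | 70% | 31% |
| 0.529 | 2.75 | 2.40 | 60% | 25% |
| 0.611 | 3.22 | 2.75 | 49% | 20% |
| 0.617 | 3.26 | 2.77 | 48% | 20% |

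**Step 3. What an observed ratio of 1.0 would leave open.**

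Upper 95% limit = 10^(1.987 × SD × 0.2535): 1.73 at SD 0.472 and 2.05 at SD 0.617.

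**Step 4. How small the SD would have to be.**

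For 90% power at a doubling with 20 against 70, the log10 SD would have to be about 0.36. Every PT value in Step 1 is larger.

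**Memory B-cells.** No variability is given, so no calculation is possible.

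**The case against.** Several points on the other side have force.

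- **The SD is inferred.** It is back-solved under two readings, from older whole-cell vaccine and MMR study data. The true spread in unboosted 9- to 10-year-olds may differ, so the ranges are conditional. Still, no positive SD makes 20 children adequate for any effect.
- **The hypothesis is directional.** The protocol expects titres to rise if circulation rises. A one-sided 5% test of 20 against 70 gives 90% power for about 2.25- to 2.9-fold, 80% for 2.0- to 2.5-fold, and 60% to 80% power for a doubling. That is milder but leaves the conclusion unchanged.
- **Individual titres are also read.** This helps, but no cut-off is given. Even 0 of 20 recently infected is compatible with 1 − 0.05^(1/20) = 13.9% infected (one-sided 95% bound) or 1 − 0.025^(1/20) = 16.8% (two-sided exact).
- **The equal-means statement is useful.** It supports comparing 10-year-old controls with 9-year-old baselines, since age alone should not shift titres. It fails only as a reason for the number 20.

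A reader might go further and infer three things that the document does not support.

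1. *That the plan will declare circulation absent if the test is non-significant.* No such rule is written. The stated purpose of excluding the effect points that way, but it can also mean separating circulation from the vaccine effect.
2. *That one-year persistence in general would be wrongly credited to the booster.* Section 9 compares boosted children with same-age controls at one year. Both groups lived through the same season, so that contrast is largely net of circulation. The exposure lies mainly in the within-child changes.
3. *That the one-year t-test of 20 against 60 is itself a test of circulation.* It compares boosted with unboosted children. A null result there would mean no demonstrated booster difference.

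**Conclusion.** The adequacy claim is unsupported as written, and for PT it disagrees with the variability implied by the protocol's own power statement. For log10 SD 0.47 to 0.62, two-sided 5%, and 20 controls against 70 pre-booster children, the design has:

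- 90% power for a PT geometric mean ratio of about 2.5- to 3.3-fold;
- 80% power for about 2.2- to 2.8-fold;
- 48% to 70% power for a true doubling.

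These figures hold for PT only and rest on carrying the back-calculated SD over to this age group. For memory B-cell responses the claim has no quantitative basis in the protocol.

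Severity is should-fix. No stated number is miscalculated, the control group is ancillary to a largely descriptive study, and the concurrent one-year comparison protects much of the inference. But the text claims a property that the design does not have, and correcting it is cheap.

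**What to change.** 1. In Sample size calculation, replace the claim about any effect with the actual capability, for example: *With 20 controls and 70 pre-booster children, a two-sided 5% test has 90% power for a PT geometric mean ratio of about 2.5- to 3.3-fold (80% for 2.2- to 2.8-fold), assuming a log10 SD of 0.47 to 0.62. No such statement can be made for memory B-cell responses.* If the sponsor has the SD from its own 2007 data in this age range, use that instead and recompute.
2. Report the control versus pre-booster geometric mean ratio with its 95% confidence interval.
3. State that a non-significant result does not exclude a smaller circulation effect, and that this limits the reading of the within-child changes from pre-vaccination to one year.
4. Base the one-year booster effect on the concurrent boosted versus control comparison already planned in Section 9.
5. Keep the equal-geometric-means statement as support for comparing 9- and 10-year-olds, and remove it as the reason for 20.

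Cost: protocol wording and one reported interval. No extra children, samples or visits are needed. The stated capability becomes less favourable.
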